### 390 *Biochemical variables*

391 Morning fasting blood samples will be obtained from each child by experienced nursing  
392 staff in the Clinical Trials Unit of TECNALIA (HUA, Vitoria-Gasteiz). Blood samples  
393 will be immediately centrifuged, aliquoted within one hour collection and stored at -70  
394 °C or below. This permits measurements of glucose, insulin, lipid profile (total-, HDL-  
395 and LDL-cholesterol, and TG), liver enzymes (ALT, AST and gamma-GT), leptin,  
396 adiponectin, C-reactive protein, thyroid hormones (TSH, T3 and T4), urea, bilirubin and  
397 uric acid.

### 398 *Physical fitness*

399 Physical fitness includes cardiorespiratory fitness, muscular strength and speed agility.  
400 A high level of physical fitness is associated with cardiovascular health in children (52).  
401 Moreover, changes in cardiorespiratory fitness in response to exercise could be good  
402 predictors of changes in cardiovascular disease risk factors (27).

403 Physical fitness will be assessed using valid and reliable tests for young people (53, 54)  
404 (more information on [www.thealphaproject.net](http://www.thealphaproject.net)). All the tests will be performed twice  
405 and the best score will be recorded except cardiorespiratory tests, which will be  
406 performed only once. Muscular fitness will be assessed by means of the handgrip  
407 strength and standing long jump tests (55). Speed-agility will be assessed with the  
408 4x10m shuttle run test (56). Cardiorespiratory fitness will be assessed by two different  
409 tests: (a) The 20m shuttle run test (57) in which the equation reported by Léger et al.  
410 (57) will be used to estimate the maximum oxygen consumption ( $VO_{2max}$ , ml/kg/min)  
411 from the 20m shuttle run test scores, and (b) Direct cardiopulmonary exercise  
412 progressive incremental treadmill test using the modified American College of Sports  
413 Medicine protocol with respiratory gas analysis to exhaustion (32). The test starts with a  
414 6% slope and increases by 1% per minute with a fixed speed of 4.8 km/h (3.0 mph)  
415 (Treadmill Ergelek, Vitoria-Gasteiz, Spain). Children will be familiarized with the

416 treadmill ergometer prior to testing. Children will be encouraged to walk to the limit of  
417 their tolerance during the test. Metabolic gas exchange will be measured breath by  
418 breath throughout the test using a metabolic cart (monitor Ergo CardMedi-soft S.S,  
419 Belgium Ref. USM001 V1.0), and data will be averaged each 60 seconds. Heart rate  
420 will be monitored at rest, continuously throughout the test, and for 5 minutes in the  
421 recovery period using a 3-lead electrocardiogram (Med Card Stress MEDISOFT). The  
422 exercise electrocardiogram will be monitored continuously. Blood pressure will be  
423 measured at rest and three times in the recovery period (minutes 1, 3 and 5). Children  
424 will report their perceived exertion according to the self-reported rating (from 0 to 10)  
425 of perceived exertion Omni-scale (58) at the end of each minute. True maximum  
426 oxygen consumption ( $VO_{2max}$ ) will be verified using the American College of Sports  
427 Medicine exercise testing criteria. The exercise test will continue until the child decides  
428 to stop or until  $VO_{2max}$  is reached. Participants who do not achieve these criteria will be  
429 classified as having reached the  $VO_{2peak}$ . Subsequent analysis will account for this  
430 factor. The exercise test will be supervised by a physician and the result of the  
431 electrocardiogram obtained during the test reviewed by a cardiologist to ensure that  
432 there are no medical conditions that limit or advise against the participation in the  
433 exercise program.

434         The cardiopulmonary exercise test will be used to obtain objective and direct  
435 measurements of peak aerobic capacity and peak heart rate, and to determine ventilatory  
436 thresholds. Exercise intensities are established according to two different criteria:  
437 individual ventilatory thresholds (first ventilatroy threshold, VT1, and second ventilator  
438 threshold, VT2) and percentages of  $HR_{max}$ . The VT1 can be determined by analyzing  
439 the slope of the carbon dioxide production ( $VCO_2$ ) vs.  $VO_2$  relationship, identifying as  
440 the point of transition in the  $VCO_2$  vs.  $VO_2$  slope from less than 1 to more than 1, or by

the ventilator equivalent of  $\text{VO}_2$  vs. work rate relationship, identifiable as the nadir of the relationship. The VT2 is identifiable as the nadir of the ventilator equivalent ratio of  $\text{VCO}_2$  vs. work rate relationship. The identification of the two ventilatory thresholds will determine the different exercise intensity domains: (a) light to moderate exercise intensity when HR values are below VT1; (b) moderate to high or vigorous exercise intensity if HR values are between VT1 and VT2, and (c) high to severe intensity exercise intensity when HR values are from VT2 to peak intensity. When the VT2 is not possible to identify, exercise intensity domains will be established taking into account the percentages of  $\text{HR}_{\text{max}}$ , *i.e.*, moderate intensity is defined between 64% and 75 % of  $\text{HR}_{\text{max}}$ , vigorous intensity from  $\geq 76\%$  to  $< 96\%$  of  $\text{HR}_{\text{max}}$  and near to maximal from  $\geq 96\%$  to 100%  $\text{HR}_{\text{max}}$  (32).

Exercise intensities are established according to the percentages of maximum heart rate as follows: moderate intensity is defined between 64% and 75 % of maximum heart rate, vigorous intensity from  $\geq 76\%$  to  $< 96\%$  of maximum heart rate, and near to maximal from  $\geq 96\%$  to 100% maximum heart rate (32).

#### *Psychological measures*

Changes in the psychological variables will be assessed to examine the additional effect of aerobic and strength training on self-esteem and psychological well-being in overweight and obese children.

The psychological variables will be estimated with valid and reliable questionnaires and include: anxiety, daily stress, self-concept, depression and the perception of parental feeding styles in children and parenting practices and eating behaviour in parents.

The questionnaires for children include the Spanish version of the State-Trait Anxiety Inventory for Children (59), the Children's Daily Stressors Inventory (60), the Self-concept form-5 Questionnaire (61), the translated version of the Children's Depression

466 Inventory (62) and the adapted Spanish version of Parental Feeding Styles  
 467 Questionnaire (63). The State-Trait Anxiety Inventory for Children measures chronic  
 468 symptoms of anxiety and contains 20 items asking the frequency in which children  
 469 experience anxiety symptoms such as “I am scared”, “I feel troubled” and “I get a funny  
 470 feeling in my stomach” using three-point scales: 1= *almost never*, 2= *sometimes* and 3=  
 471 *often*. A total trait anxiety score is calculated by summing the ratings for all items. The  
 472 Children’s Daily Stressors Inventory assesses the daily stress referring to the worries  
 473 and setbacks that occur in the everyday lives of school-age children. This self-report  
 474 inventory includes 22 dichotomous items covering the areas of health and  
 475 psychosomatic problems, stress at school and stress in family context. The score is  
 476 obtained by adding the total of positive answers. Higher scores indicate children  
 477 experienced more stress. The Self-concept form-5 Questionnaire is a questionnaire for  
 478 measuring the self-concept in five dimensions: (a) Academic self-concept refers to the  
 479 personal beliefs about the quality of the performance as a student, (b) Social self-  
 480 concept is the perception of the performance in social relations, (c) Emotional self-  
 481 concept is one’s understanding of his/her emotional state as well as his/her responses to  
 482 specific situations when certain degree of commitment and involvement is necessary in  
 483 everyday life, (d) Family self-concept refers to the children’s perception in his/her  
 484 involvement, participation and integration in the family environment, and (e) Physical  
 485 self-concept is one’s beliefs about his/her physical appearance and his/her physical  
 486 condition. The Self-concept form-5 Questionnaire contains 30 statements on a scale  
 487 from 0 (*Totally disagree*) to 99 (*Totally agree*). The Children’s Depression Inventory  
 488 assesses the severity of self-reported symptoms of childhood depression. Subscales  
 489 include negative mood, interpersonal difficulties, ineffectiveness, negative self-esteem,  
 490 and anhedonia. These items can be assessed on a 3-point scale: 0 (*absence of*

491 *symptomatology*), 1 (*mild symptomatology*), or 2 (*severe symptomatology*). The total  
492 score ranges between 0 and 54 points. Finally, the Parental Feeding Styles  
493 Questionnaire is used to measure children's perception of the feeding styles shown by  
494 parents. This questionnaire contains 26 items and includes four subscales (i.e.,  
495 Emotional feeding, Instrumental feeding, Control, and Encouragement). The Parental  
496 Feeding Styles Questionnaire can be answered on a five-point Likert scale ranging from  
497 1 (*Never*) to 5 (*Always*) according to the frequency in which the situation described  
498 happened. The higher the score, the higher the feeding style at issue.

499 The questionnaires for parents include the Parent-Child Relationship Inventory (64) and  
500 the Three Factor Eating Questionnaire(65). The Parent-Child Relationship Inventory  
501 assesses parents' attitudes toward parenting and toward their children. The Parent-Child  
502 Relationship Inventory is a 78-items self-report questionnaire answered in a four point  
503 Likert scale ranging from 1 (*Strongly agree*) to 4 (*Totally disagree*). The statements  
504 considered in this questionnaire are grouped into seven scales: (a) Social and emotional  
505 support, (b) Satisfaction with parenting, (c) Involvement, (d) Communication, (e) Limit  
506 setting, (f) Autonomy, and (g) Role orientation. High scores on the different scales  
507 indicate greater agreement with the situation defined in each scale. The Three Factor  
508 Eating Questionnaire is a 51-item self-report questionnaire that assesses three different  
509 dimensions of eating behaviour: (a) Cognitive Restraint, (b) Disinhibition, and (c)  
510 Hunger. The questionnaire has two parts; in the first part, participants answer 36  
511 statements with *true* or *false*. In the second part, participants are asked to circle the  
512 response appropriate to them. Scores can range from 0 to 21 for the restraint scale, from  
513 0 to 16 for the disinhibition scale and from 0 to 14 for the hunger scale.

#### 514 **Potential confounders**

##### 515 *Pubertal development*

516 Pubertal development will be directly assessed according to Tanner criteria (genital  
517 development and pubic hair) by the paediatricians in the Paediatric Endocrinology Unit  
518 of the HUA.

519 *Physical activity, sedentary behaviour and dietary assessment*

520 Both the control and the exercise groups will attend the same healthy lifestyle education  
521 program. However, differences in changes in physical activity level, sedentary  
522 behaviour and dietary habits could be potential confounders on the effect of the  
523 intervention on hepatic fat and cardiometabolic risk factors.

524 Physical activity will be objectively measured by accelerometry. Children will be asked  
525 to wear an accelerometer on their non-dominant wrist (wActisleep-BT, USA) for seven  
526 consecutive days all the time, except for water-based activities. Thresholds will be used  
527 to classify raw counts per minute into intensities of physical activity (66). Information  
528 about sleep duration and quality will be also obtained from the accelerometers.

529 Participants will also complete a diary log. A self-reported sedentary behaviour  
530 questionnaire (67) will be administered to the children. Participants will report the  
531 frequency of specified sedentary behaviours using predefined response categories  
532 separately for weekdays and weekends. Behaviours to be assessed include watching TV,  
533 playing computer games, playing video games or phone games, surfing the Internet for  
534 recreation, surfing the Internet for study purposes, and studying (nonschool time).

535 Dietary intake will be evaluated by two non-consecutive 24h recalls within a period of  
536 seven days. Children will report all their food and beverage ingestions assisted by  
537 nutritionists. Moreover, dietary habits and patterns will be evaluated by two different  
538 food frequency questionnaires: the KidMed index for the children (68) and a validated  
539 food frequency questionnaire for the parents or caregivers (69). The KidMed index was

540 developed to estimate adherence to the Mediterranean dietary pattern in children and  
541 young adults, based on foods/dietary patterns that sustain it.

#### 542 *Socio-demographic variables*

543 A parental questionnaire will be used to collect information about socioeconomic status,  
544 demographic characteristics, neonatal data of the children and family medical history of  
545 obesity, diabetes, dyslipidemia and hypertension. The Family Affluence Scale will be  
546 used as an index of socioeconomic status. The Family Affluence Scale is an indicator of  
547 affluence *versus* material deprivation and describes family expenditure and  
548 consumption based on 4 items: having an own bedroom, number of cars per family,  
549 number of PCs at home and internet access(70). The Family Affluence Scale has been  
550 widely used as an index of socioeconomic status(71, 72). Other indicators of  
551 socioeconomic status will be used: the parental education level (primary school,  
552 secondary school/technical training or university degree), and parental occupation  
553 according to the International Standard Classification of Occupation  
554 (<http://www.ilo.org/public/english/bureau/stat/isco/index.htm>). Demographic  
555 characteristics will include date of birth, sex, ethnicity and family structure. Perinatal  
556 data will include weight (g), length (cm) and head circumference at birth (cm),  
557 gestational age (weeks), and duration of both breastfeeding and exclusive breastfeeding  
558 (months).

#### 559 *Assessment of side effects*

560 We will record adverse effects or health problems attributable to the testing sessions or  
561 exercise sessions. Particularly we will report those attributable to the exercise sessions  
562 such as muscle pain, fatigue, and general aches and pains by self-report during the study  
563 period and the occurrence of anxiety, depression or disordered eating or behaviors by  
564 self-report or parental report. An independent researcher will be in charge of auditing all  
565 assessment staff to record all these events in the participants over the study period.

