## Randomization

Eligible participants will be randomly assigned after completing the baseline measurements to either the control or exercise groups (Figure 1). Randomization of the participants into control or exercise group will be computer generated using IBM-SPSS-Statistical software. Assessment staff will be blinded to participant randomization assignment.

[figure not shown]

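### Physical complaints are recorded only when attributed to testing or exercise sessions, so ascertainment differs by arm; the named recorders appear to be the blinded assessment staff

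*Protocol*

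**What the plan says.** The Protocol, under Assessment of side effects, sets the general rule: "We will record adverse effects or health problems attributable to the testing sessions or" exercise sessions. It then puts the weight on one source: "exercise sessions. Particularly we will report those attributable to the exercise sessions", with muscle pain, fatigue and general aches as examples, taken by self-report. The same sentence adds "period and the occurrence of anxiety, depression or disordered eating or behaviors by" self-report or parental report. This last item is worded by occurrence and not by cause.

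The section closes on who does the work. An independent researcher audits ("self-report or parental report. An independent researcher will be in charge of auditing all"), and the sentence continues "assessment staff to record all these events in the participants over the study period".

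Three other sections bear on this:

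- **Randomization:** "Assessment staff will be blinded to participant randomization assignment".
- **Exercise training intervention:** exercise sessions are for the exercise group, three days a week for 22 weeks.
- **Rationale and design of the education interventions:** both groups attend 11 sessions, one every two weeks.

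**The concern.** There are two problems, and both concern what is collected and by whom.

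First, an event enters the record only after someone has linked it to a session. A control child has no exercise sessions. An ache or a tired week in that child can qualify only if it is tied to a testing session. The control count of exercise-attributed complaints is then zero by rule and not by observation. Under Study design, the Protocol justifies its control group by the fact that growing children change anyway. The same reasoning applies to aches and fatigue, yet the recording rule removes the comparison for them. A harm that nobody expected, and so nobody attributed, would be lost in either arm. No later analysis plan can recover events that were never written down.

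Second, if assessment staff are the recorders, they must log events defined by attendance at exercise sessions, and such an entry tells them the child's arm. Some of the outcome work depends on effort or judgement. On the treadmill, for example, "Children will be encouraged to walk to the limit of" their tolerance. An assessor who knows the arm can influence such a result without meaning to.

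**Working it through.** **Step 1. Which events can be recorded in which arm.** The recording rule is set against the sections that say who attends what.

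| Event type | Exercise arm | Control arm |
|---|---|---|
| Attributed to a testing session (baseline and after 22 weeks, both arms) | recorded | recorded |
| Anxiety, depression, disordered eating (worded by occurrence) | recorded | recorded, on a reasonable reading |
| Muscle pain, fatigue, aches attributed to exercise sessions | recorded | cannot arise |
| Same complaints, not attributed to a session | not recorded | not recorded |
| Other health problems not attributed to a session | not recorded | not recorded |

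The first two rows can be compared between arms. The third is asymmetric by construction, and the last two are lost.

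**Step 2. How easily the asymmetry looks like an effect.** The Protocol states no event rate, so there is no figure of its own to reproduce. This step is an illustration.

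Inputs from Sample size calculation: 80 recruited per arm, 64 per arm after 20% loss (80 × 0.80 = 64).

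Assumptions: the true rate *p* of a complaint is the same in both arms; in the exercise arm every complaint is attributed to exercise; in the control arm none can be.

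With *r* events against 0 and *n* per arm, the two-sided Fisher p-value is 2 × C(n, r) / C(2n, r).

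- n = 80, r = 5: 0.059
- n = 80, r = 6: 0.028
- n = 64, r = 5: 0.058
- n = 64, r = 6: 0.028

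Six recorded events against none is therefore enough in both cases. The chance of reaching six is P(X ≥ 6) with X ~ Binomial(n, p):

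| True rate in both arms | n = 80 | n = 64 |
|---|---|---|
| 5% | 21% | 10% |
| 10% | 82% | 63% |
| 20% | >99% | 99% |

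If only half of the complaints in the exercise arm are attributed to exercise, the recorded rate is p/2. A true rate of 10% then behaves like 5% in the table (21% with 80 per arm), and a true rate of 20% like 10% (82%). The result depends on the attribution share, but the direction of the bias does not.

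**Step 3. Who records.** The closing sentence under Assessment of side effects allows two readings.

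- **Assessment staff record and the independent researcher audits them.** This is the natural reading. It conflicts with the blinding stated under Randomization for any child with an exercise-attributed event.
- **The independent researcher records, using the audit to collect events.** No conflict with blinding then follows.

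The Protocol does not say which is meant.

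**Step 4. How far unblinding would reach.** It needs a child with a recorded exercise-attributed event and a recorder who also assesses outcomes for that child. The Protocol does not say that these roles coincide. The encouraged treadmill test is exposed if they do, and so is the manual correction of visceral fat segmentation if the same staff carry it out. For the primary outcome, the multi-echo fat map is computed inline by software and is largely insulated.

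**The case against.** The strongest reply is that the section describes the tolerability of the exercise programme and not a safety comparison. The objectives, the secondary outcomes and the data analysis plan contain no between-arm test of adverse events. The false difference in the illustration is therefore one that a reader of the results would draw, not one that the plan computes. This stands. It limits the consequence, but the collection gap remains.

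A reader might infer that harms are recorded only if attributed, and so that the arms cannot be compared on safety at all. The Protocol does not support this. Testing sessions take place in both arms. Anxiety, depression and disordered eating are worded by occurrence. Trait anxiety and depression questionnaires, blood pressure, liver enzymes and bone density are also measured in both arms before and after.

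A reader might also infer that the blinding statement and the side-effects section flatly contradict each other. That goes too far, because the sentence names an independent researcher who may be the recorder. Further, if aches also occur without training, a bare report of an ache does not reveal the arm. Only the link to an exercise session does. A child may mention training to an assessor whoever keeps the harms record, so some risk remains in any trial of this kind.

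Finally, the downstream effect is uncertain. Dietary recalls are assisted by nutritionists and listed as a potential confounder, and the treadmill test is supervised by a physician with maximal effort checked against criteria. What is left is that the general rule filters events by attribution, and that the recorder is not clearly named.

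**Conclusion.** The point holds in a limited form. The general recording rule makes ascertainment of muscle pain, fatigue, aches and similar complaints depend on the arm, and it leaves events not attributed to a session unrecorded in both. This follows from the text and needs no assumption. Its numerical size does: the chance of a spurious difference runs from about 10% to over 99% for equal true rates of 5% to 20% with 64 or 80 per arm and full attribution, and is smaller with partial attribution.

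The tension with blinding holds on the natural reading of an ambiguous sentence. It would touch only children with an exercise-attributed event whose recorder also assesses their outcomes, and it hardly threatens the multi-echo MRI measure of hepatic fat. The matter should be corrected because collection cannot be repaired afterwards, but it does not undermine the primary analysis.

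**What to change.** Reword Assessment of side effects along these lines:

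- Record all adverse events in both arms, whatever the presumed cause.
- Use the same short checklist, with the same questions, at the 11 fortnightly sessions that both arms attend.
- Have it given by staff of those shared sessions (educators or the psychologist) or by the independent researcher. Trainers should not collect it, because they see only the exercise arm and would bring back unequal ascertainment. Blinded outcome assessors should not collect it either.
- Judge relatedness to exercise or testing afterwards, and report events by arm.
- Name the recorder, so that the section agrees with the blinding statement under Randomization.

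The cost is a few minutes per session and more unrelated events to list. The sessions already exist, so no new visits are needed.
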